### Outcome measurements

#### Primary outcome

##### Asthma Quality of Life Questionnaire (AQLQ)

In this study, the standard version of AQLQ will be used [24]. This questionnaire measures the functional problems that are most troublesome to adults with asthma over the 2 weeks prior to the interview. The AQLQ contains 32 items: activity limitation (11 items), symptoms (12 items), mental health (5 items), and environmental stimuli (4 items). Responses are rated on 7-point Likert scales for every item. High scores indicate a better health-related quality of life. The mean score of all 32 items is the overall AQLQ score. The minimum clinically important difference for AQLQ has been reported as 0.52 [25].

#### Secondary outcomes

##### Asthma Control Test (ACT)

Asthma control will be evaluated using the Asthma Control Test (ACT) [26, 27]. The ACT consists of five items: activity limitation, daytime shortness of breath, awaking due to asthma symptoms, needed puffs of reliever medication, and a global judgment of asthma control. All items refer to the last 4 weeks. They are scaled from 1 to 5. The sum of scores indicates asthma control. An ACT score of 20–25 indicates controlled asthma and of < 20 indicates uncontrolled asthma. A minimum clinically important difference of about 3 was identified [28].

##### Peak Expiratory Flow (PEF) and Forced Expiratory Volume in 1 s (FEV1)

PEF and FEV1 are determined using spirometry and body plethysmography before and after bronchodilation with a short-acting bronchodilator in accordance with recommendations of the national guidelines [29, 30].

The Self-rating Anxiety Scale (SAS) [31] and the Self-rating Depression Scale (SDS) [32] are used to assess the emotion of asthma patients. In addition, the asthma diary including the times, severity, duration of asthma attacks, medication compliance during the trial, and the first time to use the emergency medicine after treatment will also be recorded.

AQLQ and ACT will be evaluated at baseline (week 0), after the intervention (week 4), and at the follow-up (week 8, week 12). The PEF, FEV1, SAS, and SDS will be assessed at baseline (week 0), after the intervention (week 4). The asthma diary will be assessed during the whole trial (week 0– week 12). The expectation for efficacy in patients will be evaluated at baseline [33]. The first time to use emergency medicine after treatment will be evaluated during the follow-up. All the outcome evaluations will be performed by two independent outcome assessors. The two assessors are trained before participating in this trial and blinded to the randomization.

### Data monitoring and management

All data will be managed with printed and electronic Case Report Forms (CRFs). Primary entries are not allowed to be changed and any correction should be explained with a signature in the appended notes. Only outcome assessors have access to CRFs, and double-data entry will be performed. The research team in Chengdu is responsible for all aspects of the organization. The Ethics Committee of the First Affiliated Hospital of Chengdu University of TCM will be supervising this trial and data every 3 months and will make the final decision to terminate the trial. The process will be independent from investigators and the sponsor. Interventionists will monitor adverse events and respond appropriately with encouragement and suggestions. All researchers, physicians, and related personal are required to understand and adhere to protocol details.

### Data analysis

All data will be analyzed by an independent statistician using SAS 9.4 software (SAS Institute Inc., Cary, NC). All efficacy and safety analyses will be strictly conducted according to the intention-to-treat (ITT) principle. Multiple imputation will be used to deal with missing data. Continuous variables will be described with means and standard deviation (SD) or median, maximum, minimum, P25, and P75, as appropriate. And categorical variables will be described with percentage and frequencies.

The comparison between groups will be analyzed by the analysis of covariance (ANCOVA) if the change of outcomes from baseline to 4 weeks is normally distributed. The outcome variable will be the change of AQLQ from baseline to week 4, and covariates will be age, gender, duration of disease, and the expectation of acupuncture in the ANCOVA analysis. The non-parametric ANCOVA will be conducted if the change is not normally distributed. The comparisons between time points within groups will be analyzed using the paired sample *t* test or Wilcoxon rank-sum test, as appropriate. Separate ANCOVA analyses will be performed for each secondary outcome, the AQLQ and ACT at week 8 and week 12 follow-up. Categorical variables will be analyzed using the chi-squared test or Fisher’s exact test, as appropriate.

The center effects will be included in the analysis model. A subgroup analysis between inpatient and outpatient participants in each group will be performed exploratively. Statistical results will be presented as point estimates of effect sizes accompanied by confidence intervals.

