## Method and design

### Study design

A two-arm, multi-center, randomized controlled trial will be conducted at the First Affiliated Hospital of Chengdu University of Traditional Chinese Medicine (CDUTCM) and the First Affiliated Hospital of Anhui University of Traditional Chinese Medicine. Sixty-eight eligible asthma patients diagnosed with the guide for asthma management and prevention of updated GINA 2019 [2] will be recruited and randomized into two groups with a 1:1 ratio. Outcome assessment will be performed at the baseline and the end of treatment and during the follow-up period. Patients enrolment will be started in November 2019 and is expected to end in October 2021. The details of the study design are shown in Fig. 1.

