**Table 1 Tab1:**
[figure not shown]
Standard Protocol Items: Recommendations for Interventional Trials (SPIRIT) schedule of the trial

This is a randomized controlled trial which includes a 2-week baseline period, a 4-week treatment period, and an 8-week follow-up period. In the baseline period, recruited patients will be screened, and eligible asthma patients will sign an informed consent and receive a physical examination. After allocation, the patients will receive 12 sessions of acupuncture (acupoint of Lung meridian or Heart meridian) during the treatment period. The outcome assessments, AQLQ, and ACT are performed at baseline, at the end of treatment, during the follow-up, and at the end of the follow-up. The outcome assessments, PEF, FEV1, SAS, and SDS are performed at baseline and at the end of treatment. In addition, the asthma dairy should be recorded at any time during the trial if asthma attacks. The first time of emergency medicine taken should be recorded at any time during the follow-up period. The expectation of acupuncture will be assessed at baseline. The physical examination including blood routine test and blood biochemical test will also be performed at the end of treatment to evaluate risks correlated with acupuncture. Adverse events will be recorded at any time during treatment

*AQLQ* Asthma Quality of Life Questionnaire, *ACT* Asthma Control Test, *PEF* Peak Expiratory Flow, *FEV1* Forced Expiratory Volume in 1 s, *SAS* Self-rating Anxiety Scale, *SDS* Self-rating Depression Scale, *EM* Emergency Medicine

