### Sample size

According to a previous study that investigates the therapeutic effect of acupuncture for asthma [23], the mean improvement of the AQLQ was − 2.75 ± 4.52 (mean ± SD) in the acupuncture group and 0.86 ± 4.95 in the control group. With a two-side significance level of α = 0.05 and power of 80%, 27 participants are required in each group. Allowing for a 20% dropout rate, 34 participants per treatment arm will be recruited, equaling 68 patients in total.

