### Patient safety

Participants with fainting, infection, or other severe adverse events should be discontinued from treatment and processed immediately. Any adverse events will be recorded by patients, acupuncturists, and outcome assessors. Acupuncture related adverse events include bleeding, dizziness, pain, infection, and so on. Besides, any other severe events also will be recorded in the CRFs in detail and be monitored by the Ethics Committees.

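### Strict intention to treat for safety keeps never-needled patients in the adverse event denominator and slightly understates absolute risk

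*Protocol article*

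**What the plan says.** The Data analysis section puts efficacy and safety under one rule: "All efficacy and safety analyses will be strictly conducted according to the intention-to-treat (ITT) principle". The next sentence adds, without limiting it to any type of outcome, "Multiple imputation will be used to deal with missing data". No separate safety set of exposed patients is defined anywhere in the article.

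Three other statements bear on how this rule works for adverse events:

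- Needling follows randomisation. The legend of Table 1 (SPIRIT schedule) says "After allocation, the patients will receive 12 sessions of acupuncture".
- Collection is tied to the treatment period. The same legend says "Adverse events will be recorded at any time during treatment".
- The named events are consequences of needling. The Patient safety section says "Acupuncture related adverse events include bleeding, dizziness, pain, infection, and so on".

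The Sample size section sets the number randomised at 34 per arm, "Allowing for a 20% dropout rate".

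**The concern.** Intention to treat protects an efficacy comparison because it keeps the groups as randomised. A safety table mainly asks something else: how often events occur among people who were exposed. A patient who is allocated and leaves before the first session can hardly contribute a needling-related event, yet the strict rule keeps that patient in the denominator. Each such patient lowers the reported rate and none can raise it, so the error in absolute risk runs only towards understatement.

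This is more than a detail left to an unseen analysis plan. The article chooses the safety population and reinforces the choice by calling it strict, so a later safety set based on exposure would contradict it. What is at stake is the accuracy of the adverse event rates. The Discussion says the trial's results will help decide whether a full definitive trial goes ahead.

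**Working it through.** **Inputs**

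- Randomised per arm: 34 (Sample size), allocated 1:1 (Study design).
- Dropout allowance: 20% (Sample size). This is overall loss, not failure to start.
- k, the number randomised but never needled per arm: not given. Assumed 0 to 7.
- True rate of acupuncture-related events among treated patients: not given. Assumed 20%, with 10% and 30% as a range.

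**The plan's own figure first.** The Sample size section states: "With a two-side significance level of α = 0.05 and power of 80%, 27 participants are required in each group". The difference is 0.86 + 2.75 = 3.61, and the pooled SD is √((4.52² + 4.95²)/2) = 4.74. The normal-approximation formula 2 × (SD × (1.96 + 0.84)/difference)², with unrounded normal quantiles, gives 27.06 per arm. That is 28 if rounded up; power at 27 is 79.9%, so the stated figure is reproduced closely enough. Then 27/0.8 = 33.75, or 34 per arm and 68 in total. The denominator of 34 stands.

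**Dilution.** If never-treated patients have no needling-related events:

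rate under strict intention to treat = treated rate × (34 − k)/34, so the relative loss is k/34.

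| k per arm | Relative loss | True 10% reads | True 20% reads | True 30% reads |
|---|---|---|---|---|
| 0 | 0% | 10.0% | 20.0% | 30.0% |
| 1 | 2.9% | 9.7% | 19.4% | 29.1% |
| 2 | 5.9% | 9.4% | 18.8% | 28.2% |
| 3 | 8.8% | 9.1% | 18.2% | 27.4% |
| 5 | 14.7% | 8.5% | 17.1% | 25.6% |
| 7 | 20.6% | 7.9% | 15.9% | 23.8% |

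The last row is a ceiling: 34 − 27 = 7 is the whole dropout allowance, all lost before session 1.

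**No events seen.** The one-sided 95% upper limit is 1 − 0.05^(1/n): 8.4% for n = 34, 8.9% for n = 32 (k = 2) and 10.5% for n = 27 (k = 7).

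**Between the arms.** With equal k, both rates shrink by the same factor. For example, true rates of 20% and 10% with k = 2 in each arm read 18.8% and 9.4%: the ratio stays at 2, and the difference falls from 10.0 to 9.4 points. With unequal k, a difference can appear where none exists. At a true 20% in both arms and never-treated patients in one arm only, the spurious difference is 20.0 − 18.8 = 1.2 points for k = 2 and 20.0 − 15.9 = 4.1 points for k = 7.

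**The case against.** The strongest reply is that the effect is likely to be negligible. Screening, consent and the physical examination fall in a two-week baseline period before allocation, which should limit the number who never start. With one or two such patients per arm, an assumed 20% rate moves by about one point or less, while the 95% margin on 34 patients is 1.96 × √(0.2 × 0.8/34), about 13 points either way. No safety endpoint is among the listed outcomes. Individual events are recorded by patients, acupuncturists and assessors, with ethics committee oversight, whatever the denominator. A report that gives the number treated beside the number randomised lets a reader recover the exposed rate. All of this stands and keeps the severity low. It does not remove the point: the stated denominator is still the wrong one for a risk of exposure.

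A reader might infer more than the article supports:

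- *That the rule pulls the arms together.* Not in general. Balanced non-starting leaves the risk ratio unchanged, and unbalanced non-starting can create a difference. Both arms receive acupuncture, so there is no untreated arm to blur against.
- *That every event rate is multiplied by 0.8.* The 20% is overall dropout, and the factor applies only to events that need needling. The Patient safety section also covers any other adverse events, which an unneedled asthma patient can have.
- *That adverse events will be imputed.* The article does not say so. An event nobody reported is not normally a missing value, and the imputation sentence fits scheduled measurements more naturally. It is an ambiguity worth closing.
- *That patients will be needled at the other arm's points.* Nothing suggests this. The allocation goes directly to unblinded, experienced acupuncturists. Grouping by the point set received is a precaution.

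**Conclusion.** The point holds at low severity. The article's explicit rule places randomised but never-needled patients in the denominator for acupuncture-related adverse events, so absolute risk is understated by a relative k/34 in each arm. That is zero if everyone starts treatment, about 0.6 to 1.2 percentage points for one or two non-starters at an assumed 20% rate, and at most 4.1 points if the whole dropout allowance never starts. The direction follows from the arithmetic, given that never-needled patients have no needling-related events. The size rests on k and an event rate, neither of which the article states. The efficacy analysis and the sample size are not affected.

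**What to change.** In Data analysis, limit the intention-to-treat sentence to efficacy and add one on safety. It should say that adverse events will be analysed in all patients who received at least one acupuncture session, grouped by the point set actually received, using events as observed, and that multiple imputation does not apply to adverse events. Reporting the numbers randomised and treated per arm beside the safety table would make any difference visible.

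The cost is one sentence. The downside is that safety and efficacy tables may have different denominators. If every patient starts treatment as allocated, the two populations are the same and nothing changes.

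### The primary ANCOVA of change in AQLQ omits baseline AQLQ from its covariates, which costs precision and leaves chance baseline imbalance uncorrected

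*Protocol article*

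**What the plan says.** The Data analysis section of the protocol article defines the primary response: "The outcome variable will be the change of AQLQ from baseline to week 4". It then names the adjustment terms: "covariates will be age, gender, duration of disease, and the expectation of acupuncture in the ANCOVA analysis". A later paragraph of the same section adds one more: "The center effects will be included in the analysis model". Baseline AQLQ is not named as a model term there or anywhere else in the article.

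The value is available. Under the outcome measurements the article states: "AQLQ and ACT will be evaluated at baseline (week 0), after the intervention (week 4), and at the follow-up (week 8, week 12".

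For the other outcomes the Data analysis section says "Separate ANCOVA analyses will be performed for each secondary outcome, the AQLQ and ACT at week 8 and week 12 follow-up" and gives no covariates for those models.

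The Randomization and allocation concealment section describes no stratification or minimisation on AQLQ, so balance on it is left to chance.

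**The concern.** Subtracting the baseline is not the same as adjusting for it. If the two measurements have equal variances and a correlation below 1, change is negatively correlated with the starting value: patients who start low tend to gain more. A model of change without the baseline value leaves that variation in the residual, and it does not correct for whichever arm happens to start lower.

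The protocol names its covariates rather than leaving them to a later document. An analysis plan that follows the text would fit the less precise model, and adding baseline AQLQ once data had been seen would be an unplanned change to the primary analysis. The trial has 68 patients and compares two active acupuncture prescriptions. Its result is meant to inform whether a definitive trial goes ahead, so the width of the primary confidence interval matters.

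**Working it through.** **Inputs from the protocol (Sample size section).** Acupuncture group: "the mean improvement of the AQLQ was − 2.75 ± 4.52 (mean ± SD". Control: "0.86 ± 4.95 in the control group". Design: "With a two-side significance level of α = 0.05 and power of 80%, 27 participants are required in each group". After 20% dropout, 34 per arm are recruited.

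**Assumed input.** The correlation r between baseline and week-4 AQLQ is not in the documents. It is varied from 0.3 to 0.9, with equal variances at the two times.

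**Step 1: reproduce the plan's figure.**
- Difference: 0.86 − (−2.75) = 3.61.
- Pooled SD: √[(4.52² + 4.95²)/2] = 4.74.
- Standardised effect, in SDs of change: 3.61/4.74 = 0.762.
- n per arm = 2 × (1.960 + 0.842)² / 0.762² ≈ 27.06, which matches the stated 27 to the nearest whole number.
- 27/0.80 = 33.75, so 34 per arm and 68 in total.
- Power at 27 per arm: 0.80 by the normal approximation, 0.784 by the t distribution. The t value is the reference below.

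**Step 2: effect of adjustment on variance.** With score variance s² at each time:
- Variance of change: 2(1 − r)s².
- Residual variance after adjusting for baseline: (1 − r²)s².
- Ratio: (1 − r²)/[2(1 − r)] = (1 + r)/2.

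After adjustment the standardised effect becomes 0.762/√[(1 + r)/2]. The t-based power at 27 per arm follows.

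| r | Variance ratio | Fall in SE | Adjusted effect | Power, unadjusted | Power, adjusted |
|---|---|---|---|---|---|
| 0.3 | 0.65 | 19% | 0.945 | 0.78 | 0.93 |
| 0.5 | 0.75 | 13% | 0.879 | 0.78 | 0.89 |
| 0.7 | 0.85 | 8% | 0.826 | 0.78 | 0.85 |
| 0.9 | 0.95 | 2.5% | 0.781 | 0.78 | 0.80 |

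A simulation of 8,000 trials at each r, with 27 per arm, gave 0.79 unadjusted and 0.92, 0.88, 0.84 and 0.80 adjusted. It charges the adjusted model the degree of freedom it spends.

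**Step 3: effect of a chance baseline difference.** If the arms differ at baseline by D, the change-score estimate moves by −(1 − r)D. With all 34 per arm analysed, as under intention to treat with imputation, one standard error of the baseline difference is √(2/34) = 0.243 SD of the score. The size of the shift is (1 − r) × 0.243:
- r = 0.3: 0.17 SD
- r = 0.5: 0.12 SD
- r = 0.7: 0.07 SD
- r = 0.9: 0.02 SD

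These are SDs of the score, whereas 0.762 is in SDs of change. One SD of change equals √[2(1 − r)] score SDs, that is 1.18, 1.00, 0.77 and 0.45 at the four values. As a share of the planned effect the shifts are therefore about 19%, 16%, 12% and 7%. For example, at r = 0.5, 0.121/(1.00 × 0.762) = 16%.

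All results are in SD units or ratios, so they do not depend on the scale of the AQLQ figures in the Sample size section.

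**The case against.** The strongest defence is that nothing is broken. In a randomised trial the comparison of changes is unbiased over repeated randomisations and keeps its type I error. Regression to the mean is, in expectation, equal in the two arms. All of this stands. A reader might infer from the omission that the primary estimate is biased or the test invalid. The documents do not support that: the shift in Step 3 is conditional on the imbalance that happens to occur.

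A reader might also infer that the trial is underpowered because of the omission. It is not. The Sample size section uses SDs of change with no baseline adjustment, which matches an unadjusted comparison of changes, and its 27 per arm reproduces. Adjustment buys power beyond the plan.

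The size of the gain is uncertain. With the same questionnaire repeated after four weeks and background inhaled steroid dose held stable, r could be high, and at 0.9 the gain is slight. At 0.3 it is large. The listed covariates and centre may already recover part of it if they correlate with baseline AQLQ; the figures ignore that.

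Two further readings go beyond the text. One is that the secondary and week 8/12 models use the same covariates; the section suggests this but names none for them. The other is that baseline AQLQ is left out of the multiple imputation; the article does not specify the imputation variables, so no fault can be found there.

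Finally, centre appears outside the covariate sentence, so that sentence alone is not the whole model. But the section does name the terms, and baseline AQLQ is in neither place. If it was intended, the text still needs correcting.

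**Conclusion.** The point holds as a matter of efficiency and of protection against chance imbalance; it is not a question of validity. The primary model, as written, omits a covariate that is already collected. Under equal variances and r between 0.3 and 0.9, including it would cut the variance of the treatment comparison by 35% to 5% and raise power at 27 per arm from 0.78 to between 0.93 and 0.80. It would also remove a conditional shift of 0.17 to 0.02 SD of the score for a one-standard-error baseline difference. The benefit is material for r up to about 0.7 and small near 0.9. The sample size stands. For the secondary and follow-up analyses the point is conditional on their using the same covariate set. The change should be made, but the trial is not unsound without it.

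**What to change.** Add baseline AQLQ to the prespecified covariates of the primary ANCOVA, keeping the four named covariates and centre. State which covariates the secondary and week 8/12 ANCOVAs use. If they are the same set, add to each model the baseline value of the outcome it analyses. Make the change before any outcome data are examined by arm. The cost is one phrase in the text and one degree of freedom per model; for AQLQ, ACT, PEF, FEV1, SAS and SDS the baseline values are already scheduled at week 0.

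### The Wilcoxon rank-sum test, made for independent samples, is named for paired comparisons over time within each arm; the signed-rank test is the one that fits (minor)

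*Protocol article*

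**What the plan says.** In the protocol article, the Data analysis section introduces the within-arm analyses with "The comparisons between time points within groups will be analyzed using the paired sample" t test, and offers as the other option the "Wilcoxon rank-sum test, as appropriate". The signed-rank test is not mentioned anywhere in the article.

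The closing paragraph on outcome measurements sets the assessment times. AQLQ and ACT are taken at weeks 0, 4, 8 and 12. PEF, FEV1 and the anxiety and depression scales are taken at weeks 0 and 4. All are repeated measurements on the same patients.

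Comparisons between the two arms are handled separately in the Data analysis section, by ANCOVA on the change from baseline, with this fallback: "The non-parametric ANCOVA will be conducted if the change is not normally distributed".

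**The concern.** A comparison of two time points within one arm is a comparison of each patient with himself or herself. The sentence recognises this in its parametric option, which is a paired test. Its non-parametric option does not: the rank-sum test treats the two sets of scores as if they came from different people.

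The rank-sum reference distribution is therefore too wide when a patient's scores are positively correlated, and real changes over time would be missed. One table could also hold a valid paired p-value for one outcome and an invalid unpaired one for the next, depending only on which branch each outcome took.

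**Working it through.** **Can the sentence be read another way?** Between-arm comparisons already have their own methods (ANCOVA or its non-parametric form), so the rank-sum test cannot be meant for those. The words after the test name choose between the two tests listed and do not bring in a third.

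**Number of patients (Sample size section).** The plan states: "With a two-side significance level of α = 0.05 and power of 80%, 27 participants are required in each group". Inputs: mean changes of −2.75 (SD 4.52) and 0.86 (SD 4.95).
- Difference: 2.75 + 0.86 = 3.61.
- Pooled SD: √((4.52² + 4.95²)/2) = √22.47 = 4.74.
- n per arm: 2 × (1.96 + 0.84)² × 22.47 / 3.61² ≈ 27.1. Normal-approximation power at 27 is 79.9%, so the stated 27 is reproduced within rounding.
- Dropout: 27 / 0.8 = 33.75, rounded up to 34, as stated.

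These figures are used here only to set n; none is disputed.

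**Why the test is mis-sized.** With n pairs and no true change, the variance of the rank-sum statistic is, in large samples, (1 − ρs) times the variance that the test assumes, where ρs is the rank (Spearman) correlation between the two time points. The true two-sided level at a nominal 5% is then 2Φ(−1.96 / √(1 − ρs)). For bivariate normal data ρs = (6/π) arcsin(r/2):
- r = 0: ρs = 0, level 5.0%.
- r = 0.3: ρs = 0.288, 1.96/0.844 = 2.32, level 2.0%.
- r = 0.5: ρs = 0.483, 1.96/0.719 = 2.72, level 0.6%.
- r = 0.7: ρs = 0.683, 1.96/0.563 = 3.48, level 0.05%.

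**Simulation at the trial's size.** Bivariate normal pairs, two-sided nominal 5%, 20,000 data sets per scenario. The correlation r and the shift of 0.5 SD are assumptions; the protocol gives neither. Where two values are shown, they are the spread over repeated simulations.

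| n | r | True level, rank-sum | Power, rank-sum | Power, signed-rank |
|---|---|---|---|---|
| 34 | 0 | 4.6–4.8% | 50% | 49% |
| 34 | 0.3 | 1.8–2.3% | 51% | 65% |
| 34 | 0.5 | 0.7–0.9% | 50% | 79–80% |
| 34 | 0.7 | 0.07–0.08% | 52% | 94% |
| 27 | 0 | 4.7% | 42% | 41% |
| 27 | 0.3 | 2.2% | 40% | 54% |
| 27 | 0.5 | 0.8% | 39% | 69% |
| 27 | 0.7 | 0.09% | 38% | 88% |

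The true level of the signed-rank test stays between about 4.5% and 5% in every row. The rank-sum test gains nothing from the pairing: its power barely moves with r, while that of the signed-rank test rises steadily.

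**The case against.** The strongest reply is that this is a naming slip. The same sentence names the paired t test, an independent statistician will do the analysis, and the Quality control section says that statistics experts reviewed the protocol. The signed-rank test may well be what is run. That is plausible and keeps the point minor, but the published text still names the wrong test and needs the same correction.

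The second reply concerns the figures. Normal data would presumably go to the t test, so the simulation does not represent the data for which the non-parametric branch exists. The correlations and the shift are also not the trial's. Both points stand: the table is an illustration, and at zero correlation there is almost no error. The direction is firmer, because the (1 − ρs) factor depends on the rank correlation and not on normality.

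Three stronger readings are tempting, and the document does not support them:
- **That the trial's main result is at risk.** It is not. The week-4 AQLQ comparison, the secondary outcomes and the follow-up comparisons between arms all use ANCOVA or its non-parametric form.
- **That false positives would rise.** With positive within-patient correlation the rank-sum test is conservative, so they would fall.
- **That the plan will claim efficacy from within-arm p-values, neither arm being untreated.** The Data analysis section says only that these comparisons will be made. It draws no inference about efficacy from them, so a required statement that they are descriptive would answer a claim that the plan does not make.

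**Conclusion.** The sentence is wrong as written, and the matter is minor. An independent-samples test is named for paired data, and nothing elsewhere in the article corrects it. If it is followed literally, p-values in the non-parametric branch of the within-arm comparisons are wrong whenever repeated scores are correlated, and too large when that correlation is positive, as repeated scores on one patient ordinarily are. The loss runs from almost nothing at zero correlation to, at r = 0.7 and 34 patients, a true level under 0.1% and power of about 52% where 94% was available. These sizes rest on assumed correlations, an assumed 0.5 SD shift and normal data. No power target is set for these comparisons, and no comparison between the arms depends on them.

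**What to change.** In the Data analysis section, replace rank-sum with signed-rank in the sentence on comparisons between time points within groups. No other change is needed. The cost is one word: no new data, no change to the sample size and no change to the between-group analyses. If a separate statistical analysis plan exists, it should name the same test.
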